#### Risk Notification and Education

Two days after completing the baseline survey, all participants will be sent a hyperlink to the education website, Do I Have Prediabetes? [18]. This will be delivered as an iframe in a Qualtrics survey; in this way, we will be able to measure the number of participants who actually visit the website and the duration of time they spend on the site. After visiting the website, participants will be asked about which pages of the website they visited, what they learned, and what they liked and disliked about the website.

#### Mobile 360° Video

Four days after completing the baseline survey, participants randomized to the mobile 360° video arm will be sent the first video; 2 days later, they will be sent the second video. Up to 2 reminder texts 1 day apart will be sent to individuals who do not access the links for the videos. Similar to the educational website, the videos will be delivered as an iframe within a web-based survey. This will allow us to assess the duration of time spent watching the video and to collect immediate feedback on participants’ impressions of each video.

#### MAPS Phone Calls

A health coach trained in MAPS will call the participants randomized to that group; the first call may be used to initiate MAPS coaching or to simply schedule the upcoming MAPS counseling sessions. Participants will be offered up to 5 coaching calls over 4 weeks, each lasting approximately 10 minutes. During these sessions, participants will explore their motivation and goals and how enrollment in the DPP LCP may fit with these goals. Additionally, MAPS coaches will help participants identify barriers to achieving their goals and troubleshoot ways to address these barriers. If a participant enrolls in the DPP LCP, any remaining MAPS calls will serve to reinforce the positive change the individual has made, provide accountability, address ongoing challenges and barriers, and encourage continued engagement with the DPP LCP. All MAPS sessions will be audio-recorded, and at least 1 session per week per coach will be reviewed by a MAPS expert. Feedback will be provided to coaches as needed. This process will insure the fidelity of the MAPS intervention. Participants will have the option to tell the MAPS coaches that they would like to stop receiving calls at any point.

#### Offer to Refer to DPP LCP

Ten days after study enrollment, all participants will be sent a single question survey: “Would you like the DPP LCP to call you to help you enroll?” The contact information for participants who respond “yes” will be sent to the referral coordinator at their respective health system's DPP LCP, who will then call them to enroll. The rationale for this piece of the intervention is to mimic the current workflow for individuals to enroll — in most cases, a health care provider places a referral to the program via the EHR, and the program contacts the potential participant to enroll them. Due to the COVID-19 pandemic, both study sites have been offering the DPP LCP virtually, either as an asynchronous online program or through synchronous group sessions. During the study, participants will have the ability to select whatever DPP LCP format they prefer, including in-person sessions, if available.

#### Follow-Up Survey

The follow-up survey will be sent via text message to all participants 4 weeks after the baseline survey is completed. The survey will include all of the items described in the baseline survey (diabetes-related knowledge, beliefs about the controllability of diabetes, self-efficacy, and risk perceptions). The survey will conclude with a 9-item questionnaire about the practical barriers and facilitators that were relevant to choosing whether to enroll in the DPP LCP such as perceptions of the need for counseling to change one's lifestyle (which prior work suggests many individuals don't feel the need for) [28]; accessibility of the DPP LCP in terms of cost, location, time requirements, and scheduling [29]; and desire to participate in an online vs in-person DPP LCP [30,31]. This portion of the survey will provide space for free-text comments on each barrier and also ask for input on other barriers we did not anticipate. At the end of the follow-up survey, participants will be asked if they are willing to participate in a short phone-based semistructured interview about their experiences in the study. We will randomly select up to 40 individuals for these interviews; those who are interviewed will receive a US $20 electronic gift card.

We will use Qualtrics survey software for all questionnaires used in this study [32]. This platform allows us to automate the timing and delivery of each intervention component. This platform will allow us to assess the number of people contacted and the click rate of participants in each intervention component. Finally, the platform also provides a mechanism for participants to easily opt out of the trial at any time by responding “STOP” to any text message.

Each participant will be sent US $20 electronic gift cards upon completion of the baseline survey and follow-up survey (US $40 total for the study). To motivate completion of all study procedures, participants who complete both the baseline and follow-up questionnaires will be placed into a lottery for 1 of 5 US $100 electronic gift cards.

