**Methods:**

We will conduct a 3-armed randomized clinical trial comparing enrollment and 1-month engagement in the DPP LCP among adults with prediabetes from 2 health care settings. Participants in the best-practice condition will receive SMS-based notifications that they have prediabetes and a link to a website that explains prediabetes, T2DM, and the DPP LCP. This will be followed by a single question survey, “Would you like the DPP LCP to call you to enroll?” Participants in the 2 intervention arms will receive the same best-practice intervention plus either 2 mobile 360° videos or up to 5 brief phone calls from a health coach trained in a motivational coaching approach known as Motivation and Problem Solving (MAPS). We will collect measures of diabetes-related knowledge, beliefs in the controllability of risk for T2DM, risk perceptions for T2DM, and self-efficacy for lifestyle change pre-intervention and 4 weeks later. The primary outcomes of the study are enrollment in the DPP LCP and 4-week engagement in the DPP LCP. In addition, data on the person-hours needed to deliver the interventions as well as participant feedback about the interventions and their acceptability will be collected. Our primary hypotheses are that the 2 novel interventions will lead to higher enrollment and engagement in the DPP LCP than the best-practice intervention. Secondary hypotheses concern the mechanisms of action of the 2 intervention arms: (1) whether changes in risk perception are associated with program enrollment among participants in the mobile 360° video group and (2) whether changes in self-efficacy for lifestyle change are associated with program enrollment among participants in the MAPS coaching group. Finally, exploratory analyses will examine the cost effectiveness and acceptability of the interventions.

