#### Aim 1.3

To examine the mechanism of the MAPS intervention by comparing changes in DPP LCP–related self-efficacy across study arms**,** we will calculate the changes in self-efficacy across all 3 treatment groups using the scoring procedures described by Wilson et al [26]. We will then use a similar mediation procedure to the aforementioned to determine if the efficacy of MAPS is mediated by changes in self-efficacy for DPP LCP enrollment and engagement and self-efficacy for health behavior change as hypothesized [37]. Our hypothesis is that if MAPS increases participants’ self-efficacy, then enrollment in the DPP LPC will increase.

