## Discussion

In this project, we will conduct a 3-arm randomized controlled trial intended to compare the efficacy of a best-practice approach and 2 novel interventions on enrollment and engagement in the DPP LCP. These interventions will be delivered directly to individuals with prediabetes through their mobile phones. To standardize the offer of referral to the DPP LCP, all participants will receive an offer to be referred to the National DPP LCP 10 days after completing the baseline survey. Our primary outcome will be participants' enrollment and 1-month engagement in the National DPP LCP.

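### Risk perception and self-efficacy are re-measured only at week 4, 18 days after the referral offer, so for an unknown share of enrollees the mediator is measured after enrollment

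*Protocol article*

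**What the plan says.** All references are to the Protocol article.

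- **When the mediators are measured.** The abstract gives two time points: "self-efficacy for lifestyle change pre-intervention and 4 weeks later". Follow-Up Survey fixes the second: "The follow-up survey will be sent via text message to all participants 4 weeks after the baseline survey is completed". It adds: "The survey will include all of the items described in the baseline survey", which covers risk perceptions and self-efficacy. No measurement of either scale is described in between. The feedback collected after each video concerns impressions of that video, not the risk perception scale.
- **When enrollment can happen.** Offer to Refer to DPP LCP: "Ten days after study enrollment, all participants will be sent a single question survey". The Discussion counts the same interval from the baseline survey: "all participants will receive an offer to be referred to the National DPP LCP 10 days after completing the baseline survey". A coordinator then calls those who say yes. By Table 1, enrollment is registering (in person) or setting an app password (online).
- **Enrollment inside the four weeks is provided for.** MAPS Phone Calls: "If a participant enrolls in the DPP LCP, any remaining MAPS calls will serve to reinforce the positive change".
- **What the analysis tests.** The section headed Aim 1.2 applies the Baron and Kenny procedure to changes in affective and experiential risk perception. The section headed Aim 1.3 uses a similar procedure to determine "if the efficacy of MAPS is mediated by changes in self-efficacy for DPP LCP enrollment and engagement". (Aims and Objectives numbers these two aims 1.1 and 1.2.)
- **What threat is acknowledged.** Aim 1.2 concedes that sequential ignorability may fail because of unmeasured confounders, and adds a structural mean model and principal stratification for that reason. Time order is not mentioned there or in Limitations.

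**The concern.** A mediator has to change before the outcome it is said to produce. Here a participant can accept the offer, register, and only then complete the scales whose change is taken to explain the registration. Registering may itself raise self-efficacy or alter perceived risk. In the MAPS arm there is a further route, because calls held after enrollment turn to reinforcement, accountability and continuing barriers, all before self-efficacy is re-measured.

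Nearly all enrollees are expected in the two active arms. Any effect of enrolling on the scales would therefore produce both an arm difference in the mediator and a mediator-outcome association, which are the two paths the mediation procedure looks for. A shift in the opposite direction could offset a genuine mediated effect. At stake are the two mechanism aims and the secondary hypotheses in the abstract. The problem is clearest for enrollment, since 4-week engagement is mostly reached after the survey.

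**Working it through.** **1. Timeline.** Videos go out on days 4 and 6, the offer on day 10, MAPS calls run over 4 weeks, and the survey is sent on day 28. Gap between offer and mediator measurement: 28 - 10 = 18 days.

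**2. Inputs from Sample Size and Power Calculation.** Enrollment 2% (best practice), 32% (video), 45% (MAPS); 80, 160 and 160 participants; alpha 0.05 (two-sided assumed). Expected enrollees: 80 × 0.02 = 1.6; 160 × 0.32 = 51.2; 160 × 0.45 = 72.

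**3. The plan's own figure reproduces.** Power = Φ[(difference - 1.96 × pooled SE) / unpooled SE].
- Video: (0.30 - 1.96 × 0.0567) / 0.0401 = 4.71.
- MAPS: (0.43 - 1.96 × 0.0631) / 0.0423 = 7.23.

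Both give power above 99.99%, in line with the stated figure of more than 99%. This point disputes no stated number.

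**4. Simulation with zero true mediation.** Enrollment Y depends on arm only. A share f of enrollments occurs before the survey. The mediator is M = N(0,1) + d for early enrollees and N(0,1) for everyone else. Two regressions mimic the procedure: M on arm, and Y on arm plus M (linear probability with robust errors, because about 1.6 control events invite separation). **Both f and d are assumptions, because the article gives neither.** Percentages are trials with p < 0.05, from 1,000 trials per row and arm, 80 vs 160.

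| f | d (SD) | Both paths, video | Both paths, MAPS | Mediator-outcome only, video | Mediator-outcome only, MAPS |
|---|---|---|---|---|---|
| 0 | n/a | 0.3 | 0.5 | 6.3 | 5.9 |
| 0.25 | 0.3 | 0.5 | 0.3 | 6.8 | 6.7 |
| 0.25 | 0.5 | 0.5 | 0.8 | 13.0 | 12.6 |
| 0.5 | 0.3 | 1.4 | 1.6 | 15.8 | 16.9 |
| 0.5 | 0.5 | 2.4 | 4.3 | 29.4 | 36.0 |
| 0.5 | 0.8 | 8.8 | 17.2 | 63.8 | 69.1 |
| 0.75 | 0.5 | 7.7 | 13.6 | 63.4 | 63.0 |
| 0.75 | 0.8 | 22.7 | 39.1 | 93.2 | 95.6 |
| 1 | 0.3 | 5.3 | 7.1 | 44.3 | 49.3 |
| 1 | 0.5 | 15.5 | 30.3 | 85.0 | 88.6 |
| 1 | 0.8 | 37.9 | 64.1 | 99.8 | 99.9 |

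Repeating the 0.5 SD rows with new random numbers gave 3% (video) and 4% (MAPS) for both paths at f = 0.5, and 16% and 31% at f = 1. The mediator-outcome path alone was significant in about 29% and 37% at f = 0.5, and in 84-88% at f = 1. The differences are within simulation error (standard error at most √(0.25/1000) = 1.6 points).

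**5. Hand check of the arm-to-mediator path.** The spurious arm difference is d × f × (difference in enrollment), with standard error √(1/80 + 1/160) = 0.137. For MAPS at f = 1, d = 0.5, this is 0.5 × 0.43 = 0.215 SD, so z = 0.215 / 0.137 = 1.57 and the chance of significance is about 35%; the simulation gave 34.7%. At f = 0.5 the difference halves. This path is the bottleneck, so the both-paths figure falls quickly as f falls while the mediator-outcome path stays inflated.

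**The case against.** - **The early share is unknown and may be modest.** After day 10 a participant must answer yes, be called, and then register. The MAPS sentence is conditional: it allows for early enrollment and does not say how common it will be. This stands. A reader might infer that most enrollees will have enrolled by week 4, and so quote the 64% in the last MAPS row as the expected false-mediation rate. The article gives no enrollment dates and no shift, so that row is an extreme, and the video arm is lower in the same row (37.9%).
- **The aims are worded modestly.** Aims and Objectives speaks of comparing changes across arms, and the abstract of association with enrollment. This partly stands: comparing week-4 changes by arm is legitimate description. But the Aim 1.2 and Aim 1.3 analysis sections claim mediation of efficacy. The association wording also gives limited shelter, because the mediator-outcome path is the one most easily inflated.
- **The plan already doubts its mediation assumption and adds two causal models.** They are introduced against unmeasured confounding. Neither turns a score taken after enrollment into a cause of enrollment.
- **Week 4 is the only planned measurement after full MAPS exposure.** This stands. An earlier measurement would capture only early calls, so timing is a trade-off and not a simple oversight.
- **Only secondary analyses are affected.** This stands. A reader might infer that the trial's main result is biased, but the arm comparison of enrollment does not use the mediators.

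**Conclusion.** The point holds for the mediation analyses and no further. By the article's own schedule, enrollment can precede the only post-baseline mediator measurement by up to 18 days after the offer, and no stated rule or model deals with that order. The size cannot be fixed from the document. At an assumed 0.5 SD shift and no true mediation, both paths are falsely significant in about 3-4% of trials with half enrolling early, rising to 16% (video) and 31% (MAPS) if all do. The mediator-outcome path alone goes from about 29-37% to 84-88%, against a nominal 5%. If few enroll early, or enrolling barely moves the scales, the bias is small. The randomized comparison, sample size and power are unaffected. The documents do not support saying that the mediation results will be wrong, only that, as planned, cause and consequence cannot be told apart for participants who enrolled first.

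**What to change.** In the analysis sections headed Aim 1.2 and Aim 1.3:

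1. Use the registration or app-password date and the survey completion date to classify each enrollment as before or after the week-4 survey. This assumes the programs can supply the date along with the enrollment record.
2. Report the number enrolled before the survey, by arm.
3. Where enrollment came first, report the week-4 mediator-enrollment results as associations and not as mediation.
4. Add a sensitivity analysis by timing. Keep early enrollees in the main analysis, because excluding them selects on the outcome after randomization.

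In Limitations, add that the mediators may have been measured after enrollment.

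The cost is date handling, a few sentences and a weaker mechanism claim. No new data collection from participants is needed.

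Optional: a short mediator survey sent to all arms before the day-10 offer. It would restore the order for enrollments after it, and was still feasible for most participants when the article reported 39 started against a target of 480. It is a trade-off. It adds a risk and self-efficacy contact to every arm just before the offer that leads to the primary outcome (Limitations already names number of contacts as a possible confound), and it captures only early MAPS calls.

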### Measures

#### Outcome Measures

The primary outcomes of the study are DPP LCP enrollment and 4-week engagement, as defined by the CDC (Table 1). These data are currently collected by all CDC-recognized organizations offering the National DPP LCP and are a part of their required reporting for DPP LCP recognition.

**Table 1 table1:** Centers for Disease Control and Prevention (CDC)–defined measure of enrollment and engagement in in-person and online Diabetes Prevention Program’s Lifestyle Change Programs (DPP LCPs).

Time point	In-person	Online
Milestone 1 (enrollment)	Registration for the program	Setting their password for the app
Milestone 2 (4-week engagement)	Attending at least 2 out of the first 4 sessions	Must do at least 2 of the following activities: (1) Complete 2 education modules; (2) send at least 1 in-app message and/or Group Wall post; (3) set or log at least 1 behavior; (4) log, plan, or research at least 3 meals; (5) log physical activity at least 3 times; (6) weigh in on 3 or more days during 2 out of the first 4 sessions

The DPP LCP at University of Utah Health is covered by some insurance plans and requires an out-of-pocket fee for those without coverage. The cost for the online program is currently US $504, and the cost for the in-person program is US $425. Some scholarships are available for those who meet income guidelines. These costs may change during the course of the study. The Midvale CBC’s program is offered free of charge and is currently funded by a grant. To minimize the problem of cost as a barrier to enrollment, University of Utah Health participants who are uninsured or underinsured may be invited to participate in the Midvale CBC program. Otherwise, all other participants will only be invited to attend the program offered by their health system.

#### Process Measures

If the mobile 360° videos and MAPS are successful in increasing enrollment and early engagement with the DPP LCP as they have been in our pilot work (manuscript for the Video pilot study submitted to JMIR Diabetes, 11/26/20; manuscript for MAPS pilot in preparation), they have tremendous potential to be scaled up to help prevent T2DM nationwide. More than 80% of adults in the United States own a smartphone [33]. Therefore, health systems and DPP LCPs nationwide could implement these interventions. The scalability of the interventions depends, of course, not just on their efficacy but also on the effort that DPP LCPs must expend to implement them. Therefore, in this project, we will collect data on the person-hours required to implement each intervention at our 2 sites. This will inform our planned future work to test whether the intervention arms differ significantly in their effectiveness and cost effectiveness (Table 2).

**Table 2 table2:** Process measures collected by study staff.

Measure	How measured
Number of participants who click on educational website link	Link is sent as a Qualtrics survey question; clicking on link results in data indicating a “click” was made.
Number of participants in the mobile 360° video group who click on each of the videos and time spent watching	Click rates from survey in which video is embedded and duration of time on each video
Number of participants in the MAPS group who respond to our initial attempts to connect for MAPS	Attempts to call will be documented by the health coach using a RedCAP survey.
Number of person-hours needed to train health coaches in MAPS	Documented hours for the duration of the training including practice sessions with KL
Number of person-hours required to deliver each MAPS session	The start and end time for each MAPS session will be documented by the health system using a REDCap survey.
Number of person-hours required to oversee MAPS sessions to insure fidelity to the protocol	Documented hours for the time spent by KL to review and provide feedback on a sample of recorded MAPS sessions

### Statistical Analyses

#### Sample Size and Power Calculation

Statistical power for the primary analysis in Aim 1 was calculated using the statistical power calculation software PASS 14 [34]. Based on prior work on the effect of risk notification and education, we hypothesize that 2% of participants in the risk notification and education arm of the study will enroll in the DPP LCP. In the intervention arms, based on our pilot work, we hypothesize that enrollment in the DPP LCP will increase to 32% and 45% for the mobile 360° video and MAPS arms, respectively (manuscript for the video pilot study submitted to JMIR Diabetes, 11/26/20; manuscript for MAPS pilot in preparation). We plan for a total sample size of 400; of whom, 80 will be randomized to risk notification and education alone, 160 will be randomized to risk notification and education plus mobile 360° video, and 160 will be randomized to risk notification and education plus MAPS. We calculated that this study will have >99% power to detect the hypothesized differences between the best practice arm and the intervention arms. To address the possibility of loss to follow-up, we are planning to recruit a total of 480 individuals into the trial.

#### Aim 1

We will use logistic regression to compare the effects of the 3 treatments on the likelihood of enrollment and 1-month engagement in the DPP LCP. The distributions of participants’ demographics and baseline measures of risk perception and self-efficacy will be summarized and compared by treatment groups using chi-squared tests for categorical variables and *F* tests for continuous variables. If participants’ demographics and baseline measures of risk perception are not balanced across the 3 treatment groups at baseline, we will use inverse probability of treatment weighting with propensity scores to create a synthetic sample and compare the difference in the causal average treatment effects across the 3 treatment groups [35]. We will calculate standardized differences to check whether the distribution of baseline covariates is independent of treatment groups conditional on the propensity score. We will conduct intention-to-treat analysis to account for noncompliance. We will summarize missing data for all variables in the dataset. We will employ multiple imputation to examine the impact of any missing values in a sensitivity analysis. All analyses will be conducted using statistical programming language R, and statistical significance will be defined at alpha=.05.

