#### Allocation to Condition

After completing the baseline survey, individuals will be allocated to the condition according to randomization tables generated by the projects statistician (YZ). These tables will be based on permuted block randomization, stratified by health system and sex, with block sizes randomly generated as 5, 10, or 15. In accordance with our planned sample sizes in each arm, each block will maintain a 1:2:2 ratio in sample size across the treatment groups (best practice, mobile 360° videos, and MAPS).

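### With 1.6 expected enrollees in the reference arm, the logistic regression needs a named small-event method, because default Wald inference would fail in about 14–20% of trials run at the planning rates

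*Protocol article*

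**What the plan says.** Under Statistical Analyses, Aim 1, the protocol article gives one model for both primary outcomes: "We will use logistic regression to compare the effects of the 3 treatments on the likelihood of enrollment and 1-month engagement". It adds intention-to-treat analysis, R as the software and an alpha of .05. It names no test within the model and no method for an arm with few or no events.

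The planning values are under Sample Size and Power Calculation. For best practice, "we hypothesize that 2% of participants in the risk notification and education arm of the study will enroll in the DPP LCP". For the interventions, "we hypothesize that enrollment in the DPP LCP will increase to 32% and 45% for the mobile 360° video and MAPS arms, respectively". The sizes are "We plan for a total sample size of 400; of whom, 80 will be randomized to risk notification and education alone", with 160 in each intervention arm, and recruitment is raised to 480 to allow for loss to follow-up. Under Allocation to Condition, "each block will maintain a 1:2:2 ratio in sample size across the treatment groups", so 480 recruits means 96, 192 and 192.

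The power statement is: "We calculated that this study will have >99% power to detect the hypothesized differences between the best practice arm and the intervention arms". The hypothesized rates are for enrollment only. Outcome Measures makes 4-week engagement a primary outcome as well, and Table 1 lists it as the milestone after enrollment.

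**The concern.** Best practice is the reference group for both primary comparisons, and it is the smallest arm with by far the lowest expected rate. If nobody in it enrolls, the likelihood keeps rising as the log odds ratio grows, so no finite estimate exists. Software stops at an arbitrary large coefficient with an enormous standard error, and the Wald p-value in the coefficient table is close to 1.

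The result could then be read in opposite ways. A likelihood-ratio test would show overwhelming evidence of benefit, while the default table would show no significant difference. If the replacement method is chosen only when this is seen, it is chosen with the results in view. A trial that goes as the investigators expect should not depend on that choice.

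**Working it through.** **Inputs.** From Sample Size and Power Calculation: control rate 2%; intervention rates 32% and 45%; arms of 80, 160 and 160; 480 recruited. From Allocation to Condition: 1:2:2. From Aim 1: alpha .05, taken as two-sided because the article does not say.

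**1. The stated power reproduces.** Pooled two-proportion z test, 80 vs 160, 2% vs 32%:
- pooled rate = (80×0.02 + 160×0.32)/240 = 0.22
- null SE = √[0.22×0.78×(1/80 + 1/160)] = 0.0567
- alternative SE = √[0.02×0.98/80 + 0.32×0.68/160] = 0.0401
- power = Φ[(0.30 − 1.96×0.0567)/0.0401] = Φ(4.71), above 99.99%

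For 2% vs 45% it is higher still. Both also exceed 99.9% at alpha 0.025.

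**2. Chance of an empty reference arm.** Expected events are 80×0.02 = 1.6, or 96×0.02 = 1.92.
- 80 controls: 0.98^80 = 19.9%
- 96 controls: 0.98^96 = 14.4%

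**3. Power by test, enrollment.** Both binomials were enumerated exactly. The Wald test on the log odds ratio counts as non-significant when a cell is zero. The Firth-type test adds 0.5 to each cell, which is the Firth estimate for a two-group model, and uses a Wald statistic.

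| Arms | Rates | Wald | Likelihood ratio | Score | Firth-type |
|---|---|---|---|---|---|
| 80 vs 160 | 2% vs 32% or 45% | 80.1% | >99.9% | >99.9% | >99.9% |
| 96 vs 192 | 2% vs 32% or 45% | 85.6% | >99.9% | >99.9% | >99.9% |

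The Wald figures are almost exactly 1 minus the zero-event chance (1 − 0.199 and 1 − 0.144). The whole loss therefore comes from the empty arm.

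**4. What a fit shows.** With 0/80, 51/160 and 72/160 enrollees, an ordinary logistic fit gave intervention coefficients near 24, standard errors near 14,647 and Wald p = 0.999. These values depend on when the software stops. The likelihood-ratio statistic for the same data is 73.2 on 2 df. For 0/80 vs 51/160 the Firth-type Wald p is 0.002, and the risk difference is 31.9 percentage points (Newcombe 95% CI 23.7 to 39.4).

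With 1/80 vs 51/160 the odds ratio is (51/109)/(1/79) = 37, with 95% CI 5 to 273. With 2/80 it is 18. In both cases Wald p < 0.001.

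**5. Engagement.** The article gives no rate. If engagement requires enrollment, the control rate is at most 2%. Assume that 75% or 50% of enrollees engage in every arm. Arms of 80 vs 160:

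| Assumed rates, control vs video | P(0 of 80) | Wald | Likelihood ratio | Score | Firth-type |
|---|---|---|---|---|---|
| 1.5% vs 24% | 29.8% | 70.1% | >99.9% | >99.9% | >99.9% |
| 1% vs 16% | 44.8% | 54.2% | 99.7% | 99.4% | 98.4% |

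For MAPS (33.75% and 22.5% on the same scaling) Wald power is 70% and 55%, and the other tests exceed 99.9%. With 96 vs 192, Wald power for video is 77% and 62%.

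**The case against.** The strongest reply is that the article names no Wald test. Likelihood-ratio, score and penalised tests all count as logistic regression, and all exceed 99.9% power for enrollment. The choice among them is often left to a statistical analysis plan, which is not shown here. This stands. A reader might infer that the stated power is wrong, or that it falls to 80%. The documents do not support that: the figure reproduces, and it falls only if default Wald output is used.

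A reader might also infer that the odds ratio is never finite. It is not finite only with no control event. With one or two events the estimates are finite and clearly significant; the interval is wide, but it excludes 1 comfortably.

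A third tempting inference is that the propensity-weighted and imputed analyses must fail too. The weighted analysis is described as comparing average treatment effects, which could be risk differences and finite at 0/80. Weighting does not put events into an empty arm, however, so it does not rescue an odds ratio.

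Two further replies bear on size. Outcomes recorded by the programs need not be lost when a survey is missed, so 96 controls may be the better number; the 14.4% figure reflects this. And the risk depends on the 2% rate. At 8%, the low end of the provider-referral range in the Introduction, the chance of 0 in 80 is 0.1%. But 2% is the rate the trial chose to plan on.

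What remains is that the article fixes a model and a planning rate which, taken together, make an unworkable result under ordinary maximum likelihood reasonably likely.

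**Conclusion.** The point holds as a weakness in the chosen analysis, not as an error in the power figure. At the protocol's own rates, ordinary maximum-likelihood logistic regression meets an empty reference arm in 14–20% of trials. In those trials it gives no finite odds ratio against best practice and an uninformative default test.

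The power statement is right for enrollment under likelihood-ratio, score or penalised inference, but it is not tied to any of them and rests on enrollment rates alone. For engagement, Wald power would be about 54–70% with 80 controls, against 98% or more for the alternatives. That range assumes that engagement requires enrollment, that the control rate is 1–1.5%, and that the intervention rates shrink in proportion.

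Severity is should-fix. An unseen analysis plan may already settle the test.

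**What to change.** In the Aim 1 analysis, pre-specify Firth penalised-likelihood logistic regression with profile-penalised intervals for both primary outcomes. Likelihood-ratio inference is an acceptable alternative for the test and already restores the power, but with an empty arm it still gives no finite odds ratio.

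Report alongside it the risk difference for each intervention against best practice, with a score-type interval (Newcombe or Miettinen-Nurminen). This stays finite and readable with no control events.

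In the sample size section, state that the power above 99% refers to enrollment under the named test.

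The cost is a few sentences and a little extra analysis work in R. Conduct, allocation and sample size stay as they are.
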